### Interim analyses {21b}

No interim analyses will be performed.

### Methods for additional analyses (e.g. subgroup analyses) {20b}

To test whether the treatment effect differs by sex and ethnicity (Dutch versus other origin), we will perform secondary analyses where, in two separate models, the three-way interaction effect of sex, treatment, and time point and the three-way interaction effect of ethnicity, treatment, and time point are respectively added to the model of the primary analysis. These models will then be used to test whether the effect of treatment on relative weight change differs by sex/ethnicity, i.e. with null hypothesis H0: relative weight change at T3 in the treatment group among men—relative weight change at T3 in the control group among men—relative weight change at T3 in the treatment group among women + relative weight change at T3 in the control group among women = 0, which can be tested using an *F* test.

### Methods in analysis to handle protocol non-adherence and any statistical methods to handle missing data {20c}

Data will be analysed based on the intention-to-treat principle. The general linear model takes drop out under the missing at random assumption into account.

### Plans to give access to the full protocol, participant-level data, and statistical code {31c}

The results of this study will be disclosed unreservedly. We will register the study before start in the Dutch Trial Registry. It is intended to publish the results as soon as possible after completion of the sample analyses and data evaluation in an appropriate peer-reviewed scientific journal. Data will be made available to other researchers upon reasonable request.

## Oversight and monitoring

### Composition of the coordinating centre and trial steering committee {5d}

The coordinating study centre is the University Medical centre, Erasmus MC in Rotterdam, Department of Dietetics, Rotterdam, The Netherlands. The trial steering committee (TSC) consists of the principal investigator, the executive investigator, the participating dietitian, and the secretariat. The TSC is responsible for all aspects of study planning and will be responsible for randomisation, data registration, data management, and biostatistics. Supervision of the study will be done by the designated trial monitor who also works at the University Medical centre, Erasmus MC in Rotterdam.

### Composition of the data monitoring committee, its role and reporting structure {21a}

Because of the low risk associated with the intervention (eHealth application), no DSMB or safety committee will be established.

### Adverse event reporting and harms {22}

Adverse events are defined as any undesirable experience occurring to a subject during the study, whether considered related to the investigational product/study procedure/the experimental intervention. All adverse events reported spontaneously by the subject or observed by the investigator or his staff will be recorded.

A serious adverse event is any untoward medical occurrence or effect that.-Results in death;-Is life threatening (at the time of the event);-Requires hospitalisation or prolongation of existing inpatients’ hospitalisation;-Results in persistent or significant disability or incapacity;-Any other important medical event that did not result in any of the outcomes listed above due to medical or surgical intervention but could have been based upon appropriate judgement by the investigator.

An elective hospital admission will not be considered as a serious adverse event.

The investigator or anyone from the medical staff to whom the adverse event is reported will immediately inform the principal investigator who in his turn will inform the sponsor (head of the Department of Internal Medicine).

The investigator will report all SAEs to the sponsor without undue delay after obtaining knowledge of the events.

The sponsor will report the SAEs through the web portal ToetsingOnline to the accredited METC that approved the protocol, within 7 days of first knowledge for SAEs that result in death or are life threatening followed by a period of maximum of 8 days to complete the initial preliminary report. All other SAEs will be reported within a period of maximum 15 days after the sponsor has first knowledge of the serious adverse events.

All AEs will be followed until they have abated or until a stable situation has been reached. Depending on the event, follow-up may require additional tests or medical procedures as indicated and/or referral to the general physician or a medical specialist.

SAEs need to be reported till end of study within the Netherlands, as defined in the protocol.

[data safety monitoring board (DSMB)/safety committee].

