### Intervention description {11a}

#### The control and intervention group

Both groups will receive a VLED, with meal replacements (The 1:1 diet by Cambridge Weight Plan®), plus a stepped care approach to reintroduce a healthy and sustainable long-term diet according to national guidelines [17]. Patients will follow a VLED of approximately 3140 kJ (750 kcal)/day for 10 weeks, consisting of two meal replacements plus 75 g of lean meat/fish/vegetarian replacement, 150 ml skimmed milk, and low-energy drinks and low-carbohydrate vegetables ad libitum.

After 10 weeks, the diet is changed into a low-calorie diet of 4600–5400 kJ (1100–1300 kcal)/day, gradually increasing the intake during the following 12 weeks. After a total of 22 weeks, the participants use a diet based on national health recommendations, aimed at weight maintenance. During the entire intervention, 60 min of exercise per day is advised. We encourage long-term behavioural change by making use of behavioural therapy techniques (among others: goal setting, identifying barriers and self-monitoring). During the diet, glucose levels (fasted and postprandial) are monitored (via phone) and glucose lowering agents are adjusted accordingly, by the dieticians, diabetes nurses, and medical doctor. Moreover, antihypertensive medication is adjusted whenever the blood pressure becomes too low due to the weight loss. The process is guided by registered dieticians of the University Medical centre, Erasmus MC in Rotterdam, and dietician practice HRC.

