#### The intervention group

The eHealth application, which replaces part of the face-to-face contacts, will only be used by the intervention group. In-person contact will be limited to one individual intake meeting and three group meetings. The eHealth application is a mobile diet app, which was developed earlier and has already been pilot tested. In this app, the steps of the diet-intervention will be explained via text and infographics. Participants will receive recipes and tips useful for the different stages of the diet. Exercise is encouraged with personal goal setting, using the national guidelines for exercise [18], and challenges. Personal goal setting with respect to diet, exercise, weight, body composition, glucose levels, medication use, physical complaints, and quality of life will be used and monitored within the app. Moreover, participants will receive daily motivational messages to keep them on-track. To make the app more interactive, the participants can use a chat-function with the dietician, once a week for the first 10 weeks; thereafter, the dietitian will be available every other week for the chat feature in the app. The app is end-to-end encrypted, according to the national privacy guidelines.

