#### The control group

In this group, the participants will follow the VLED intervention and will receive one individual intake meeting, five group meetings, and four planned contact moments by mail or phone (more whenever it is necessary for glucose regulation). In this group, the motivational aspect and personal goal setting with respect to diet, exercise, weight, body composition, glucose levels, medication use, physical complaints, and quality of life will be monitored during the group meetings.

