### Strategies to improve adherence to interventions {11c}

Patients in the intervention group will receive, throughout the year, notifications in the app to promote their adherence to the intervention.

The control group will receive a phone call 1 week after the group sessions to promote adherence to the intervention.

Both groups will receive a book on healthy nutrition and lifestyle developed by the Dutch cooperation of dieticians as an incentive. This book provides additional information on a healthy lifestyle beyond the group sessions and the information in the app.

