### Relevant concomitant care permitted or prohibited during the trial {11d}

Patients will receive their usual medical care and are allowed to use all their prescribed medication. Anti-diabetic medication will be adjusted before the start of the intervention, according to the guideline demedicalisation for T2D [19]. Furthermore, medication is individually adjusted when hypo- or hyperglycaemia do often occur. Other medications such as antihypertensive medication will be adjusted as required and always in agreement with the medical team. No concomitant care will be prohibited during the study.

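### Adverse events are captured passively while contact differs by arm by design, so adverse event counts by arm may be biased by ascertainment, with direction and size unknown

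*Protocol article*

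**What the plan says.** **Capture rule.** Adverse event reporting and harms {22}: "All adverse events reported spontaneously by the subject or observed by the investigator or his staff will be recorded". The rest of that section defines serious events and sets reporting timelines. It describes no scheduled question.

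**Contact, E-VLED.** The intervention group: "In-person contact will be limited to one individual intake meeting and three group meetings". Chat with the dietician is available "once a week for the first 10 weeks; thereafter, the dietitian will be available every other week for the chat feature in the app".

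**Contact, control.** The control group: "one individual intake meeting, five group meetings, and four planned contact moments by mail or phone (more whenever it is necessary for glucose regulation". Strategies to improve adherence {11c} adds: "The control group will receive a phone call 1 week after the group sessions to promote adherence to the intervention". Whether these calls overlap the four planned contacts is not stated.

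**Glucose and complaints.** Under the heading for both groups: "During the diet, glucose levels (fasted and postprandial) are monitored (via phone) and glucose lowering agents are adjusted accordingly". Glucose levels, medication use and physical complaints are followed as part of personal goal setting, in the app for E-VLED and at group meetings for control. Section {11d} mentions hypoglycaemia as a trigger for action: "medication is individually adjusted when hypo- or hyperglycaemia do often occur". It is not listed as an outcome.

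**Setting.** Participants, investigators and medical staff are unblinded ({17a}), and there is no safety committee ({21a}).

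**The concern.** A rule based on volunteering and noticing gives a fair picture by arm only if the opportunities to volunteer and to be noticed are alike. Here the tested change is the replacement of part of the face-to-face contact, so treatment and detection channel are tied together. Being observed by staff means something different in each arm, and staff know the allocation.

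Glucose-lowering and antihypertensive drugs are adjusted during the diet, so drug-related events are foreseeable. The Discussion looks ahead to implementing the blended programme. Any adverse event table by arm in the trial report is likely to be read as evidence that less face-to-face contact is, or is not, safe. If detection differs by arm, the table cannot bear that reading, and a bias of unknown sign cannot be corrected afterwards. The primary weight endpoint is not affected.

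**Working it through.** The protocol gives no adverse event rate or detection rate, so there is no figure of its own to reproduce. The check has three parts.

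**1. Planned contacts, from the sections cited above**

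- In person: control 1 + 5 = 6; E-VLED 1 + 3 = 4.
- Control with planned mail or phone contacts: 6 + 4 = 10. If the post-session calls are additional (five, one per group meeting): 10 + 5 = 15.
- E-VLED chat opportunities, assuming chat runs for 52 weeks: 10 + (52 − 10)/2 = 31. Total 4 + 31 = 35.
- Study-visit rows of Table 1 as printed: VLED at start and weeks 10, 20, 30 and 52; E-VLED at start and weeks 20 and 52. The assessment rows list week 10 without separating the arms.

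Which arm has more opportunities to report depends on whether chat counts and is used.

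**2. Effect of unequal detection**

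Expected recorded count = n × true risk × detection probability. Take n = 40 per arm (Sample size {14}) and an assumed true risk of 30% in both arms, so 12 affected participants per arm.

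| Assumed detection, control / E-VLED | Recorded, control / E-VLED | Apparent risk ratio (E-VLED : control) |
|---|---|---|
| 0.8 / 0.8 | 9.6 / 9.6 | 1.00 |
| 0.8 / 0.6 | 9.6 / 7.2 | 0.75 |
| 0.9 / 0.5 | 10.8 / 6.0 | 0.56 |
| 0.6 / 0.8 | 7.2 / 9.6 | 1.33 |

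**3. Linking detection to contacts**

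Assume each contact after intake independently reveals an event with probability p, for p = 0.10 and p = 0.20. Detection after k contacts = 1 − (1 − p)^k. After intake, control has 9 contacts (5 + 4), and E-VLED has 3 without chat or 3 + 31 = 34 with every chat used.

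| Contacts, control / E-VLED | Control detection (p = 0.10; 0.20) | E-VLED detection (p = 0.10; 0.20) | Ratio (p = 0.10; 0.20) |
|---|---|---|---|
| 9 / 3, no chat used | 0.61; 0.87 | 0.27; 0.49 | 0.44; 0.56 |
| 9 / 9, six chats used | 0.61; 0.87 | 0.61; 0.87 | 1.00; 1.00 |
| 9 / 34, all chats used | 0.61; 0.87 | 0.97; >0.99 | 1.59; 1.15 |

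With equal true risk, E-VLED can look 44–56% safer, the same, or 15–59% worse, depending only on chat use. The model treats a mail, a call, a chat and a meeting as equivalent and leaves out the phone glucose monitoring and the app entries. It shows that the sign is open and does not estimate a size.

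**The case against.** The strongest reply has four parts.

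*Hypoglycaemia is actively watched.* A reader might infer from the capture rule that hypoglycaemia is recorded only if a patient mentions it. The documents do not support that. The rule does not mention hypoglycaemia, and phone monitoring of glucose is described under the heading for both groups. A low reading seen by staff could well count as observed. This stands. What remains is that no stated rule says when a reading, an app entry or a complaint at a group meeting becomes an adverse event record, and only control is given explicit extra contacts for glucose regulation.

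*There is no safety comparison to bias.* The objectives {7}, outcomes {12} and analyses {20a, 20b} contain none. This also stands, and it limits the consequence to descriptive reporting.

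*Some data are collected alike.* Laboratory tests, the medication questionnaire and the cost questionnaire have common time points. They give arm-neutral information on drug and health-care use, but they are not described as a source of adverse events.

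*This is article-level condensation.* How staff ask about events is often left to the full protocol. That would answer a complaint about silence. Here the article states a passive rule, and arm-dependent ascertainment follows from that rule together with the stated contact schedules.

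**Conclusion.** The point holds in a limited form. Passive capture combined with contact that differs by design means that adverse event counts by arm **may** be biased. A reader might go further and infer that the safety picture **is** biased in favour of E-VLED, because that arm has fewer meetings. The documents do not support a direction: E-VLED has less in-person and phone contact but more chat and app channels, and six used chats already equalise the contact counts in the simple model.

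The size is undetermined. The apparent ratios, 0.56 to 1.33 under assumed detection probabilities and 0.44 to 1.59 under the contact model, rest on assumed values and on chat running all year. They show only that a material spurious difference is possible either way. The matter is worth correcting because the remedy is cheap and the records would otherwise be hard to interpret. It does not touch the weight or cost endpoints.

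**What to change.** 1. Add one short, identical set of questions on adverse events and hypoglycaemia, with a defined recall window, to the digital questionnaires that go to both arms at weeks 10, 20 and 52. These reach participants whether or not the arm has a visit at that time.
2. State one rule, the same in both arms, for recording glucose readings and complaints raised in the app, in chat, by phone or at group meetings as adverse events. This concerns recording only; clinical management is unchanged.
3. Base any adverse event table by arm on the solicited answers. Keep spontaneous and observed reports for serious adverse event reporting.
4. For participants already past these time points, report unequal ascertainment as a limitation. Recruitment was due to end in July 2023 and the article appeared in October 2023, so some follow-up may be complete. A change would also need notification to, and approval by, the ethics committee ({25}).

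**Cost.** A few questionnaire items, one recording rule, one table and an amendment. Patient burden rises slightly and more non-serious events will be recorded. Recall is weak across the 32 weeks between weeks 20 and 52, so the recall window should be stated and events outside it acknowledged as not captured by this route.

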### Frequency and plans for auditing trial conduct {23}

Based on the estimated risk (negligible), we opt for minimal monitoring based on the Erasmus Medical Centre guidelines (in Dutch: Richtlijnen voor on-site monitoring in relatie tot het ingeschatte risico van de studie. Versie Erasmus Medical Centre 15 november 2012 (gebaseerd op “NFU Kwaliteitsborging mensgebonden onderzoek 2.0/okt.2012)). Monitoring will take place once yearly and will be performed by an independent researcher of the Department of Internal Medicine.

### Plans for communicating important protocol amendments to relevant parties (e.g. trial participants, ethical committees) {25}

Amendments are changes made to the research after a favourable opinion by the accredited METC has been given. All amendments will be notified to the METC that gave a favourable opinion. After the METC approves the amendment, patients already participating will be notified of the changes that will affect them.

### Dissemination plans {31a}

The sponsor/investigator will submit a summary of the progress of the study to the accredited METC once a year. Information will be provided on the date of inclusion of the first subject, numbers of subjects included and numbers of subjects that have completed the study, serious adverse events/serious adverse reactions, other problems, and amendments.

The end results of this study will be disclosed unreservedly. We will register the study before start in the Dutch Trial Registry. It is intended to publish the results as soon as possible after completion of the sample analyses and data evaluation in an appropriate peer-reviewed scientific journal.

## Discussion

Adequate weight management in patients with T2D is critical to reduce associated morbidity and mortality. Current dietary care models for T2D patients are often resource intensive. With this study, we expect to answer the question whether eHealth in combination with face-to-face coaching is as effective as face-to-face coaching on reducing weight within a VLED program. This is essential given the need for more efficient work in this patient group. Previous research on this subject is not conclusive about the effects of the use of interactive eHealth on weight reduction within a diet program in patients with T2D, and the combination of face-to-face with eHealth support is scarce to date [33–36]. Expected barrier for the study is lagging patient inclusion due to COVID 19 restrictions.

By using an RCT design, we try to minimise the influence of confounders. Nevertheless, our study has some limitations: for obvious reasons, we could not blind the patient and the dietitian to the intervention. Furthermore, we use intermediate outcome measures such as weight and HbA1c because it was not feasible in terms of patient numbers and length of follow-up to report on hard endpoints like morbidity or mortality. The strength of our study is the use of three study sites in all settings of health care, making the results widely generalizable.

The findings of this study, if successful, will lead to more knowledge about the use of eHealth in lifestyle treatment for patients with T2D, more specifically on the combination of face-to-face and eHealth support. It will also potentially lead to the implementation of this eHealth, evidence-based intervention for patients with T2D. In addition, policy makers will be better informed about using eHealth for population health management.

### Trial status

Protocol version number 4, November 12, 2020.

Start recruitment: April 1, 2021.

End of recruitment (estimated): July 1, 2023.

## Data Availability

The datasets generated and/or analysed during the current study will be available from the corresponding author on reasonable request.

## Abbreviations

AE: Adverse event
CCMO: Central Committee on Research Involving Human Subjects; in Dutch: Centrale Commissie Mensgebonden Onderzoek
DSMB: Data safety monitoring board
EU: European Union
IC: Informed consent
METC: Medical research ethics committee (MREC); in Dutch: medisch-ethische toetsingscommissie (METC)
POWER: Prevention Of Weight Regain trial (referring to the diet intervention studied in this trial)
(S)AE: (Serious) adverse event
Sponsor: The sponsor is the party that commissions the organisation or performance of the research, for example a pharmaceutical company, academic hospital, scientific organisation, or investigator. A party that provides funding for a study but does not commission it is not regarded as the sponsor but referred to as a subsidising party
T2D: Type 2 diabetes
VLED: Very low energy diet
WMO: Medical Research Involving Human Subjects Act; in Dutch: Wet Medisch-wetenschappelijk Onderzoek met Mensen
